### Secondary outcome

Change in P-selection expression (platelet activation-dependent granule membrane) at different time points: flow cytometry is used to detect the P-selection expression on platelets at different time points. The influence of aspirin/salvianolate on platelet interaction adhesion during drug concentration-time curves is analyzed. (Time frame: blood samples are acquired on day 10 before administration and 15 min, 1 h, 2 h, 8 h, and 24 h after administration.)Change in PAC-1 expression (platelet-associated complement) on activated platelets at different time points: flow cytometry is used to detect the PAC-1 expression on platelets at different time points. The influence of aspirin/salvianolate on platelet aggregation during drug concentration-time curves is analyzed. (Time frame: blood sample is collected on day 10 before administration and 15 min, 1 h, 2 h, 8 h, and 24 h after administration.)Change in P2Y12 acceptor expression on platelets at different time points (P2Y12 acceptor is a receptor for ADP and ATP coupled to G-proteins that inhibit the adenylyl cyclase second messenger system): flow cytometry is used to detect the P2Y12 acceptor expression on platelets at different time points. The influence of aspirin/salvianolate on ADP- or ATP-activated platelets aggregation during drug concentration-time curves is analyzed. (Time frame: blood samples are acquired on day 10 before administration and 15 min, 1 h, 2 h, 8 h, and 24 h after administration.)Change in phosphodiesterase (PDE) enzyme expression on platelets at different time points: ELISA is used to detect the PDE enzyme expression at different time points. The influence of aspirin/salvianolate on platelets activated by PDE enzymes during drug concentration-time curves is analyzed. (Time frame: blood samples are collected on day 10 before administration and 15 min, 1 h, 2 h, 8 h, and 24 h after administration.)

### Safety observation

Blood routine;Serum biochemistry: AST, ALT, ALP, GGT, TBIL, DBIL, IBIL, GLU, BUN, K+, Na+, Cl-, Ca2+;Urine routine;ECG.

### Adverse events

Each participant will receive safety monitoring throughout the trial. All adverse events will be forwarded to the Ethics Committee and Office of clinical trials institution. They will review all documented harms during the study and adjudicate them with regards to causality.

## Withdrawal

Patients who are lost to follow-up, have bad compliance, or use other medicine that will influence the result will be withdrawn. If a participant chooses to withdraw, a withdrawal report form will be filled out to record assessments and reason(s) for withdrawal.

## Statistical analysis plan

### Method validation

Selectivity

The chromatogram of standard sample, blank sample, additional sample, and post-administration sample should be established.(2)The matrix effect, lowest limit of quantification, and stability should be tested.(3)Standard curve and its correlated coefficients should be tested.(4)Intra- and inter-day precision and accuracy of the method defined as the relative standard deviation (RSD) were evaluated by analyzing QC samples at three different concentrations in six replicates on the same day and three consecutive validation days [21].

### PK index

#### Aspirin esterase activity

Using data from the blood sample analysis (CSA/C(ASA + SA)), we will compare the results of the three arms by ANOVA analysis.

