## Objectives

The primary objective of this study is to determine the influence of salvianolate on the activity of aspirin esterase and that of aspirin on the activity of salvianolate metabolic enzyme.

The secondary objective is to determine the PK-PD characteristics of the salvianolate and aspirin combination and analyze the correlation between the exposure level and pharmacodynamic index of the medicines.

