### Study design

We will conduct a prospectively planned, open-labeled, parallel-grouped, single-centered clinical trial with aggregated PK-PD data (Fig. 1). Eighteen participants will be randomly allocated into three arms: participants in the aspirin arm will be administered with aspirin (100 mg QD) orally; participants in the salvianolate injection arm will be injected with salvianolate (200 mg + 5% glucose injection 250 mL, i.v.); and participants in the experimental arm will be administered with aspirin (100 mg QD) orally and injected with salvianolate (200 mg + 5% glucose injection 250 mL, i.v.). All treatment courses will last for 10 days. Blood samples will be acquired before administration on days 8, 9, and 10, and after administration at 5 min, 15 min, 30 min, 45 min, 1 h, 2 h, 4 h, 8 h, 12 h, and 24 h on day 10 (Fig. 2).

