### Combination

Participants are not allowed to take any kind of TCM or western medicine with pharmacological effects of activating blood circulation, platelet aggregation, and anti-coagulation or belonging to the non-steroidal anti-inflammatory class.In case of angina pectoris, participants can take isosorbide mononitrate after approval by researchers. It is permitted to take other medicines that are not metabolized through aspirin esterase and catechins-O-methyl transferase (COMT) and the record the combination.

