### Randomization

This is a single-center clinical trial of three groups. The sample size is 18 and all participants will be distributed 1:1:1. The randomization code will be developed by the study statistician. The trial cases were divided into three processing groups. The random numbers of “trial cases” was produced by SAS random procedure: they were arranged vertically by block and randomly coded. The randomized coding of test cases was the same as that of the experimental medicine. When a participant has been enrolled, the research pharmacy will randomize the individual based on the master randomization list.

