#### Catechol-o-methyltransferase (COMT) activity

We will use the column graph method. The results of the experimental, salvianolate, and aspirin arms will be compared by ANOVA analysis.

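### The three-arm ANOVA of the aspirin-esterase ratio includes an arm that takes no aspirin, and the three-arm COMT test does not isolate the effect of aspirin

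*Protocol article*

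**What the plan says.** The primary objective (Protocol article, Objectives) is to "determine the influence of salvianolate on the activity of aspirin esterase and that of aspirin on the activity of salvianolate metabolic enzyme". These are two directed questions.

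The Primary outcome section defines esterase activity as CSA/C(ASA + SA), built only from aspirin and its metabolite, with sampling timed around the aspirin dose. COMT activity is measured with a kit.

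On the arms, Study design states "Eighteen participants will be randomly allocated into three arms" and Randomization adds "The sample size is 18 and all participants will be distributed 1:1:1". In Study design, "participants in the salvianolate injection arm will be injected with salvianolate"; Table 1 lists no aspirin for that group. The Combination section bars several drug classes during the trial, including anything "belonging to the non-steroidal anti-inflammatory class".

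The analysis for the esterase ratio is: "we will compare the results of the three arms by ANOVA analysis". For COMT it is: "The results of the experimental, salvianolate, and aspirin arms will be compared by ANOVA analysis". Neither section names a pairwise contrast.

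**The concern.** The esterase index needs aspirin in the body. In the salvianolate arm there is no study aspirin to hydrolyse, so the planned three-arm comparison includes a group in which the outcome has no meaning. Whoever runs the analysis must drop that arm or invent a value for it, and the answer depends on which.

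For COMT the difficulty is one of target. The objective asks what aspirin does to the enzyme that metabolises salvianolate, which is experimental versus salvianolate. A three-arm F test also responds to salvianolate's own effect on COMT.

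At stake is whether either primary analysis, as written, answers the primary objective.

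**Working it through.** **Inputs from the Protocol article.** N = 18 at 1:1:1, so 18/3 = 6 per arm. No alpha, SD or effect size is stated, so the choice of 18 cannot be reproduced. Assumed below: two-sided alpha 0.05, one summary value per participant, normal data, equal SD in the arms that have real values, no dropout.

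**Esterase: the sections side by side.**
1. Index = CSA/C(ASA + SA) (Primary outcome).
2. Salvianolate arm: no aspirin (Study design, Table 1) and no NSAID-class drugs (Combination).
3. So numerator and denominator are both zero or below quantification, and 0/0 is undefined. A three-group ANOVA with that arm undefined returns no result. If only trace salicylic acid is detected, the ratio is SA/(0 + SA) = 1, whatever the esterase activity.
4. Participants with a usable ratio: 6 + 6 = 12 of 18. Error df = 12 − 2 = 10, against 18 − 3 = 15 for three arms.

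**Esterase: what a filled-in value does.** Trials were simulated with no salvianolate effect (same mean and SD in the aspirin and experimental arms). The salvianolate arm was fixed at 0, fixed at 1, or left out. Share with p < 0.05, 40,000 trials per row:

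| Assumed mean | Assumed SD | Scored 0 | Scored 1 | Left out |
|---|---|---|---|---|
| 0.8 | 0.05 | 100% | 100% | 5% |
| 0.8 | 0.1 | 100% | 99% | 5% |
| 0.8 | 0.2 | 100% | 54% | 5% |
| 0.8 | 0.3 | 100% | 26% | 5% |
| 0.9 | 0.05 | 100% | 99% | 5% |
| 0.9 | 0.1 | 100% | 54% | 5% |
| 0.9 | 0.2 | 100% | 16% | 5% |
| 0.9 | 0.3 | 100% | 10–11% | 5% |

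The last row is an extreme: a ratio capped at 1 with mean 0.9 has SD at most √(0.9 × 0.1) = 0.30.

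**COMT: salvianolate acts, aspirin adds nothing.** Means in SD units are aspirin 0, salvianolate d, experimental d; the overall mean is 2d/3. Noncentrality λ = n Σ(μi − μ̄)² = 6 × (4/9 + 1/9 + 1/9)d² = 4d². The test is F(2,15) with critical value 3.68.

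- d = 1: λ = 4, rejection 0.348
- d = 1.5: λ = 9, rejection 0.677
- d = 2: λ = 16, rejection 0.908

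The experimental-versus-salvianolate contrast rejects at 5% in all three cases.

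**COMT: aspirin does act.** Let aspirin change COMT by a SD in the experimental arm relative to salvianolate, with the aspirin-only arm midway. Then λ = 6 × (a²/2) = 3a². The contrast uses the pooled error (15 df) with noncentrality a/√(2/6).

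| a (SD) | Omnibus F power | Contrast power |
|---|---|---|
| 1 | 0.27 | 0.37 |
| 1.5 | 0.55 | 0.68 |
| 2 | 0.81 | 0.90 |

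In this configuration the named contrast is both more specific and more powerful.

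**The case against.** The best defence is that the natural way to run the esterase analysis is already correct. If the salvianolate values are undefined and excluded, a two-group ANOVA of the remaining arms equals the t-test and keeps its 5% level. The sampling times, tied to the aspirin dose, and the objective both point to the two aspirin-taking arms. This supports the remedy, but it departs from the text, which specifies three arms.

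Second, the documents give no half-life, background salicylate level or quantification limit, and an inclusion criterion refers to regular aspirin or salvianolate use in the prior month. Trace salicylate in the salvianolate arm cannot be excluded. That stands. A reader might infer that the test is guaranteed significant; the documents do not support this. It needs the empty arm scored 0, which no section proposes. Scored 1, rejection can be as low as 10–11%.

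Third, COMT is measurable in all three arms, and an analysis plan not shown could add a contrast. That also stands and makes the COMT point the weaker one. A reader might go further and say that the plan would declare a false interaction, or read a non-significant result as no interaction. The article states no such decision rule. The 35%, 68% and 91% describe the omnibus test, not a conclusion that the plan commits to.

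Finally, it is tempting to require a log-scale geometric mean ratio with a 90% interval. That is a reporting preference and sits awkwardly with a proportion capped at 1.

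**Conclusion.** The esterase analysis is wrong as written: one of its three arms has no valid value for the outcome. This follows from the definition of the index, the arm descriptions and the co-medication rule, and needs no numerical assumption. Only 12 of the 18 participants can inform the question. The rejection rates show what a filled-in value would do, and rest on the assumed means, SDs and normality.

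The COMT analysis can be run, but its only stated test mixes salvianolate's own effect with the effect of aspirin. Its rejection rates rest on assumed shifts in SD units. Naming the contrast is a clear improvement at no cost, not the repair of an analysis that cannot be done.

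**What to change.** - **Aspirin esterase activity:** replace the three-arm comparison with experimental versus aspirin only (6 v 6). State that the ratio is not analysed in the salvianolate arm.
- **COMT activity:** keep measuring COMT in all three arms, and name experimental versus salvianolate as the primary contrast. The aspirin-only arm can be reported descriptively.
- **Both:** report an estimated difference with a confidence interval, on a scale suited to the measure (for the ratio, one that respects its limit at 1).

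The cost is analysis wording only: no new participants, samples or assays. The esterase comparison should be described as resting on 12 participants; 18 is the trial total. With 6 v 6, 80% power needs a difference of about 1.80 SD (10 df), and the COMT contrast needs about 1.73 SD (15 df), under the assumptions listed in the working.

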#### Catechol-o-methyltransferase (COMT) activity

We will use the column graph method. The results of the experimental, salvianolate, and aspirin arms will be compared by ANOVA analysis.

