## Discussion

A combination of salvianolate and aspirin may provide an effective and safe therapeutic option for patients with CHD; however, its DDI mechanism remains unclear. We investigate this inquiry by applying a PK-PD model. Research and clinical practice become intimately intertwined on the ground of PK-PD trials. We apply typical research instruments (e.g. randomization, control) to achieve the ultimate clinical objective, to reliably and empirically determine the best therapeutic choice for patients, and also meet the aims of innovative and timely research. This study establishes a PK-PD model to determine the PK-PD characteristics of the salvianolate and aspirin combination and analyze the correlation between exposure level and pharmacodynamic index of the medicines.

Metabolic enzymes play an important role in pharmacokinetics DDI. The main metabolic enzyme is CYP450, which is essential for the metabolism of many drugs. According to statistics, CYP450 isoforms are responsible for the oxidative metabolism of approximately 85% of the marketed drugs [22]. However, neither aspirin nor salvianolate injection has any relation with CYP450. Aspirin is hydrolyzed by several kinds of esterases [23–25] and the main active component of salvianolate, SAB, is metabolized by COMT. These enzymes might be the key point of pharmacokinetics DDI between aspirin and salvianolate injection. In this case, we plan to use ELISA to measure the activity of COMT and a formula containing aspirin and its metabolite, salicylic acid, to evaluate the activity of esterase. In summary, we analyze the pharmacokinetics DDI of salvianolate and aspirin through COMT and esterase, respectively, to determine the influence between the metabolic processes of each medicine. This research also explores the functional mechanism of the two medicines on the treatment of CHD. It is the trend to establish PK-PD based on functional mechanism. The function of salvianolate and aspirin is related to the inhibition of platelet aggregation and blood coagulation. Thus, we choose P-selection, PAC-1, and P2Y12 acceptor and PDE enzymes as efficacy indexes to explore their correlation with drug concentration.

Ultimately, this research, in its entirety, will provide an approach of filling the gap between science and practice, supplying evidence of DDI, and facilitating the use of medicine combination in the treatment of CHD.

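### The three-arm ANOVA neither isolates nor sizes the pairwise influences in the primary objective, and with 6 patients per arm it cannot support the Discussion's claim of a reliable therapeutic choice

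*Protocol article*

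**What the plan says.** The Objectives section of the protocol article sets the primary aim: to "determine the influence of salvianolate on the activity of aspirin esterase and that of aspirin on the activity of salvianolate metabolic enzyme". The design that serves it is stated twice, under Study design ("Eighteen participants will be randomly allocated into three arms") and under Randomization ("The sample size is 18 and all participants will be distributed 1:1:1").

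The statistical section names one between-arm method for both primary outcomes. For the esterase index: "we will compare the results of the three arms by ANOVA analysis". For COMT: "The results of the experimental, salvianolate, and aspirin arms will be compared by ANOVA analysis", together with a column graph. The PD indices get the same ANOVA comparison. PK-PD modelling and an exposure-effect correlation are also named, but the Objectives section places them under the secondary objective.

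The Discussion says that research instruments such as randomization and control are applied "to reliably and empirically determine the best therapeutic choice for patients", and that the research will end by "supplying evidence of DDI, and facilitating the use of medicine combination in the treatment of CHD".

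**The concern.** The question and the method do not match. The objective contains two separate contrasts: combination versus aspirin alone for the esterase index, and combination versus salvianolate alone for COMT. The F-test asks whether any of the three arms differ. A significant result may come from a difference between the two single-drug arms, which is not the question. A non-significant result, with 6 patients per arm, leaves a wide range of interactions open. In neither case does the test say how large the interaction is.

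At stake is what readers may take from the trial. The article presents the work as a basis for combining the drugs and uses the word reliably. Without the size of the contrast and its uncertainty, they cannot tell a small interaction from an undetected large one.

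**Working it through.** **Inputs from the article.** 18 patients, three arms, 1:1:1, so 18/3 = 6 per arm. ANOVA for each primary outcome. The article states no power, effect size, SD or alpha, so there is no design calculation to reproduce.

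**Assumptions made here.** One independent summary value per patient, equal variances, two-sided alpha 0.05. Effects are in between-patient SD units. For the ratio scale, the between-patient CV is taken as 20%, 30% or 50%.

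**1. Does the F-test isolate the question?** Take COMT. Let the combination and salvianolate arms have the same mean (added aspirin has no effect) and let the aspirin arm differ by d = 2 SD. The noncentrality is n × Σ(mean − grand mean)² = 6 × (2/3) × d² = 6 × (2/3) × 4 = 16. With 2 and 15 df the critical value is 3.68, and the F-test is significant with probability 0.91. The direct contrast, combination versus salvianolate, would be significant 5% of the time. The F-test is therefore nearly always positive when the influence asked about is zero.

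**2. What does a non-significant result mean?** For 6 versus 6 the noncentrality is d × √(6/2) = 1.732d, with 10 df and critical value 2.228.

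| True shift (SD) | Noncentrality | Power | Missed |
|---|---|---|---|
| 0.5 | 0.866 | 12.3% | about 88% |
| 1.0 | 1.732 | 34.7% | about 65% |
| 2.0 | 3.464 | 87.6% | about 12% |

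Power reaches 80% at d = 1.80. The three-arm F-test with only the combination arm shifted behaves much the same: power 11.7% at 0.5 SD, 34.8% at 1 SD and 90.8% at 2 SD, with 80% reached at about 1.72 SD.

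**3. What would an interval show?** The half-width for a difference is t × √(2/6) SD. At 95% this is 2.228 × 0.577 = 1.29 SD; at 90% it is 1.812 × 0.577 = 1.05 SD. On the ratio scale, log-SD = √ln(1 + CV²) and SE = log-SD × √(2/6). The 90% limits around an observed ratio of 1.00 are exp(±1.812 × SE):

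| Assumed CV | log-SD | SE | 90% CI | Power, 1.25-fold | Power, 1.5-fold | Power, 2-fold |
|---|---|---|---|---|---|---|
| 20% | 0.198 | 0.114 | 0.81 to 1.23 | 42% | 89% | about 100% |
| 30% | 0.294 | 0.169 | 0.74 to 1.36 | 22% | 58% | 96% |
| 50% | 0.472 | 0.273 | 0.61 to 1.64 | 12% | 27% | 63% |

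How informative a null result is depends on a CV the article does not give. A two-fold change would usually be seen at CV 20–30%; a 1.25-fold change would be missed more often than not at all three values.

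**The case against.** The strongest reply is that the article states no faulty inference. It mentions no p-value, no significance threshold and no rule that a null result means no interaction. A reader might infer from the Discussion that a non-significant ANOVA would be taken as support for combining the drugs. The text does not support that: the Background asks whether interactions are synergistic or antagonistic, so the trial looks for an interaction at least as much as it hopes to find none. That part of the reply stands.

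Three further parts stand. ANOVA is not the only analysis named, since PK-PD modelling is there too, although for the secondary objective. Alpha, contrasts and intervals may be set out in a fuller protocol or analysis plan, so their absence from an article is not in itself a fault. The 88% figure rests on an assumed shift of 0.5 SD, and large effects would mostly be found. One may add that the sentence containing reliably is a general aspiration, not a decision rule.

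What the reply does not remove is the choice that the article does state. It names the three-arm comparison as the analysis of each primary outcome, while its own objective is pairwise. ANOVA output can be made to yield differences and intervals, but the article does not direct the analyst to the two that matter. Even as aspiration, the Discussion's wording promises more than 6 per arm can deliver.

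**Conclusion.** The point holds as a mismatch between the stated objective and the stated primary comparison, and between that comparison and the Discussion's wording. The first part depends on no effect-size assumption: a three-arm F-test does not isolate or size either primary contrast. The 91% figure illustrates this under an assumed 2 SD difference between the single-drug arms. The second part is a matter of degree. Under one summary value per patient and two-sided alpha 0.05, the miss rate runs from about 88% at 0.5 SD to about 12% at 2 SD, and 80% power needs about 1.8 SD. The CVs behind the ratio-scale figures are also assumed.

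It does not follow that the trial would treat non-significance as evidence of no interaction, or that it must become an equivalence trial. The change is worth making because it answers the stated question better at almost no cost.

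**What to change.** In the statistical section, make the primary result for each outcome the relevant pairwise contrast, from one summary value per patient, with its confidence interval:

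- COMT activity: ratio of geometric means, combination versus salvianolate alone.
- Esterase index: difference in means, combination versus aspirin alone.

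Keep the three-arm ANOVA as supportive. State that a non-significant test will not be reported as absence of interaction. In the Discussion, replace the claim of reliably determining the best therapeutic choice with wording that the trial gives an exploratory estimate of the size of the interaction. An equivalence margin is optional and not part of this change.

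The cost is a few sentences and a few lines of analysis code, with no added patients or samples. The downside is that the intervals will be wide (a 90% half-width of about 1 SD) and the conclusion more modest.
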